## Sampling Frame

The sampling strategy for the evaluation is as follows. In both AP and UP, an INHP district will be selected as an intervention area while a similar non-INHP (ICDS) district will serve as comparison, giving a total of two districts sampled per state. In UP, Barabanki has been selected as the intervention district and Unnao as the control district. In AP, Karimnagar has been selected as the intervention district and Rangareddy as the control district.

The implementation approach of INHP is that of demonstrating the effect of a technical interventions package delivered through a set of best practices that are designed to maximize effectiveness in improving nutrition and health of children, and the subsequent systematic replication of these best practices.

Approximately 10% of the *Anganwadi* centers[[1]](#footnote-2) (AWCs) “covered” by INHP are demonstration sites. A demonstration site is characterised as an AWC which holds a Nutrition and Health Day, has a Community Based Organization (CBO) which is engaged in nutrition and health activities, has active change agents, has other need-based innovations which serve as the learning ground for the project. Replication is undertaken through focused and deliberate capacity building of government counterparts and systems strengthening in the remaining 90 % areas.

INHP has so far demonstrated four best practices, which have been found to be effective for service delivery and bringing about behaviour change. These are:

- Block Level resource mapping (BLRM)[[2]](#footnote-3)
- Nutrition and Health Days (NHDs)[[3]](#footnote-4)
- Change agents (CAs)[[4]](#footnote-5)
- Community Based Monitoring System (CBMS)[[5]](#footnote-6)

In this context INHP has laid out the year-wise milestones for replication. Therefore, while conducting the evaluation research, it is crucial to identify areas (blocks, sectors and AWCs) that will receive the project interventions through the replication mode. These areas identified for possible replication should then serve as a universe for sample selection, contrary to the entire district serving as a universe for sample selection.

In an intervention district, following steps will be followed to establish the universe for sample selection:

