**Sample size for baseline and endline surveys**

Sample size is calculated to detect differences in various nutrition outcomes between each intervention district and its comparison district. Assumptions in making these calculations included a statistical power of 80% to detect a difference and a significance level of 95% (alpha = 0.05). The sample size is not increased to account for a design effect, which in nutrition studies has been small or trivial. The sample size estimations for children is based on three primary outcomes: shift in average z-scores in length and weight, stunting and anemia. Calculations for the primary outcomes for children and pregnant women are found in below.

**Table 2.1. Target sample size calculations for primary nutritional outcomes in cross-sectional surveys at baseline and 24 months**

| Outcome Measure | SD or P0 | Detectable difference in means by intervention arm | Sample size  per intervention arm* |
| --- | --- | --- | --- |
| Nutritional status  Children  Shift in average z-score  12-17 months  18-23 months  Stunting (%)  12-23 months | 1.1  1.1  60% | .18 z-score  .18 z-score  Absolute reduction 6% | 587 ~600  587 ~600  1101 ~1200 |
| Anemia  Children 12-23 months    Pregnant women | 80%  50% | Absolute reduction 6%  Absolute reduction 8% | 772 ~800  633 ~800 |

*Estimated sample size rounded to nearest ‘00.

We need approximately 1200 children aged 12-23 months for nutritional status outcomes and at least 800 children for anemia. The NFHS-2 data show that the prevalence of stunting (height-for-age <-2 SD of median of reference population) among children 12-23 months was 57.5%. We estimated a minimum sample size requirement of 1101 children for the detection of 6% absolute reduction in stunting from a 60% prevalence of stunting at baseline. We rounded the target sample to 1200 children aged 12-23 months. The target 1200 sample size is also sufficient to detect a change of at least 0.18 z-score units for anthropometric z-scores.

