**Sample Selection**

In each of the 4 districts in the evaluation, rural blocks were selected for the evaluation surveys. In UP state, the intervention district of Barabanki has 16 blocks, and CARE worked in 14 of the 16 blocks in the district, all of which were rural. The evaluation study is planned for the 10 blocks where CARE has been able to start their replication strategy immediately as the other 4 blocks has too many sector supervisor vacancies. The comparison district of Unnao has 16 blocks also, 15 of which are rural. Nine blocks will be randomly selected to represent this district in the evaluation. In AP state, each district selected for the evaluation has 15 blocks. In the intervention district of Karimnagar, CARE works in 9 of the 15 blocks, and the evaluation will be conducted in these 9 CARE blocks. In the comparison district of Rangareddy, 8 blocks will be selected randomly for the purpose of this evaluation.

Each block contains 3-6 sectors, an area with 15-25 AWC and an estimated population of 20,000-25,000 persons. In the intervention districts in each state, the sampling universe for survey sample selection include only those sectors and AWC areas that were participating in CARE’s INHP-II program as replication sites. All sectors in the selected blocks will have AWC areas participating in the intervention. In the comparison districts, the sampling universe included all functioning AWC from all sectors of the selected blocks in the district.

Baseline survey

We will use multi-stage survey sampling design to achieve the targeted sample of children and women.

*Uttar Pradesh.* In the intervention district (Barabanki), 2 sectors will be randomly sampled from each block (n=20 sectors). In the comparison district (Unnao), 2-4 sectors will be randomly sampled per block in proportion to the number of AWC per block (n=20 sectors). In both districts, 3 AWC areas will be randomly sampled from each selected sector (n=60 AWC). All the women identified will be interviewed from the sampled AWC areas.

*Andhra Pradesh.* In both districts, 2-3 sectors per block will be sampled in proportion to the number of AWC per block (n=20 sectors), and 4-6 AWC areas will be randomly sampled per sector (n=110 AWC). All the women identified will be interviewed from the sampled AWC areas.

Endline survey

The same sample selection process used at baseline will be employed again at endline.

Adequacy surveys

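### Table 2.1 takes a design effect of 1 for a sample of whole AWC areas, so the stated 80% power is not supported for stunting or for the z-score shift in each age band

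*Protocol*

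**What the plan says.** The Protocol, section Sample size for baseline and endline surveys, sizes the surveys at 80% power and alpha 0.05 to "detect differences in various nutrition outcomes between each intervention district and its comparison district". On clustering it says only: "The sample size is not increased to account for a design effect, which in nutrition studies has been small or trivial". It gives no ICC, no numerical design effect and no source.

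Table 2.1 asks for 587 (about 600) children in each of two age bands for a 0.18 z-score shift, 1101 (about 1200) for stunting, 772 (about 800) for child anemia and 633 (about 800) for anemia in pregnant women. For stunting the text states a "minimum sample size requirement of 1101 children for the detection of 6% absolute reduction in stunting from a 60% prevalence of stunting at baseline".

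The section Sample Selection describes a multi-stage sample of blocks, sectors and AWC areas, in which every woman identified in a sampled AWC area is interviewed. For UP: "In both districts, 3 AWC areas will be randomly sampled from each selected sector (n=60 AWC", from 20 sectors per district. For AP it gives 20 sectors and 110 AWC areas per district.

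**The concern.** Children in one AWC area share the same worker, supervisor, food supply and village conditions, so their outcomes are likely to be correlated. The programme is itself delivered through AWC workers and sector supervisors. What matters for power is the ICC multiplied by the cluster size less one. An ICC that looks negligible can therefore still give a material design effect when about 20 children are taken from each cluster.

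If the true design effect is well above 1, the surveys have less power than stated for stunting and the age-band z-scores. A null result on growth could then be read as programme failure under a claimed 80% power that the design did not have.

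**Working it through.** **Inputs.** Power 80% and alpha 0.05 come from the sample-size section. Sidedness is not stated, but two-sided reproduces the figures. SD, prevalences and differences come from Table 2.1. Clusters per district come from Sample Selection: 60 AWCs (UP), 110 AWCs (AP), 20 sectors (both). The ICC is not in the documents, so 0.01, 0.02 and 0.05 are assumed. All results are for a single-round contrast between arms, which is what Table 2.1 sizes.

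**1. Reproducing Table 2.1 at design effect 1**
- Z-score: 2 × 1.1² × (1.96 + 0.8416)² / 0.18² = 586.2, so 587.
- Stunting, 60% v 54%: [1.96√(2 × 0.57 × 0.43) + 0.8416√(0.24 + 0.2484)]² / 0.06² = 1067.6, so 1068. With a continuity correction it is 1101, as stated.
- Child anemia, 80% v 74%: 772 without continuity correction, as stated.
- Pregnant women, 50% v 42%: 609 without and 633 with continuity correction; 633 is stated.

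All four figures are simple-random-sample results.

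**2. Room left by rounding (largest design effect, DE, that keeps 80% power)**
- Stunting: 1200/1101 = 1.09 by the stated figure, or 1200/1068 = 1.12 without continuity correction.
- Z-score bands: 600/587 = 1.02.
- Child anemia: 1200/772 = 1.55, because hemoglobin is measured in all enrolled children aged 12-23 months.
- Pregnant women: 800/609 = 1.31.

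**3. Break-even AWC-level ICC.** DE = 1 + (m − 1) × ICC, so the break-even ICC is (DE max − 1)/(m − 1), with m the number per AWC.
- Stunting, UP: m = 1200/60 = 20; 0.124/19 = 0.0065. AP: m = 1200/110 = 10.9; 0.124/9.9 = 0.0125. With the tighter 1.09 these become 0.0047 and 0.0091.
- Z-score bands, UP: m = 600/60 = 10; 0.022/9 = 0.0025. AP: m = 5.45; 0.022/4.45 = 0.005.
- Child anemia: 0.029 (UP), 0.056 (AP).
- Pregnant women (m = 13.3 and 7.3): 0.025 (UP), 0.050 (AP).

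**4. Power at assumed AWC-level ICCs**

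Stunting: power = Φ{[0.06√(1200/DE) − 1.96√(2 × 0.57 × 0.43)] / √0.4884}. For UP at ICC 0.05: DE = 1 + 19 × 0.05 = 1.95, and (1.488 − 1.372)/0.699 = 0.166, so power is 57%.

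Z-score band: power = Φ{0.18/√(DE × 2 × 1.1²/600) − 1.96}. For UP at ICC 0.01: DE = 1.09, and 2.715 − 1.96 = 0.755, so power is 77.5%.

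| Outcome, n per arm | State | ICC 0.01 | ICC 0.02 | ICC 0.05 |
|---|---|---|---|---|
| Stunting, 1200 | UP | 78% (DE 1.19) | 72% (1.38) | 57% (1.95) |
| Stunting, 1200 | AP | 81% (1.10) | 77% (1.20) | 68% (1.50) |
| Z-score band, 600 | UP | 77.5% (1.09) | 74% (1.18) | 65% (1.45) |
| Z-score band, 600 | AP | 79% (1.04) | 77.5% (1.09) | 73% (1.22) |
| Child anemia, 1200 | UP | 89% | 85% | 71% |
| Child anemia, 1200 | AP | 92% | 89% | 82% |
| Pregnant women, 800 | UP | 86% | 82% | 72% |
| Pregnant women, 800 | AP | 88% | 86% | 80% |

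**5. If the correlation sits at sector level** (1200/20 = 60 children per sector, 30 per band, either state), stunting power is 65%, 52% and 32% at the same three ICCs, and band power is 70%, 62% and 44%. The break-even ICCs for child anemia and pregnant women fall to about 0.009 and 0.008.

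**The case against.** The strongest reply is that the loss is neither uniform nor known. A reader might infer that every primary outcome is underpowered. The documents do not support that for AWC-level clustering. Child anemia will be measured in about 1,200 children per arm and not only the 800 in the table, and the 800 pregnant women exceed the 633 required. Both stay at or above 80% in AP over the whole assumed range, and in UP until the ICC is near 0.03 and 0.025. Stunting in AP keeps 81% at an ICC of 0.01. The Protocol also says that 1,200 children suffice for the 0.18 shift. Pooled over 12-23 months, the z-score formula with 1,200 in place of 600 gives 96% to 82% in UP and 97% to 91% in AP. All of this stands, and it confines the point to stunting and the separate age bands.

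A reader might also infer that confidence intervals will be too narrow and false positives too frequent. That would need an analysis that ignores clustering. The Protocol states no analysis model, and the statistical analysis plan, which may settle it, is not shown. That inference is not made here.

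Finally, a reader might hold that one district per arm undermines the comparison altogether. The Protocol is open about this. It calls the design quasi-experimental, names the districts, and says that "an INHP district will be selected as an intervention area while a similar non-INHP (ICDS) district will serve as comparison". The size of any district-by-time shift cannot be taken from the documents. What remains is a caveat on what the power statement refers to.

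The reply does not rescue the sentence itself. No ICC or source stands behind it, and the room left by rounding is too thin to make the assumption harmless.

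**Conclusion.** The concern holds for stunting at 1,200 per arm and for the 0.18 z-score shift in each 600-child band. The arithmetic of Table 2.1 is right for independent observations; the design-effect assumption is what lacks support. The break-even ICCs follow from the Protocol's own numbers, with equal cluster sizes taken for simplicity. The power losses rest on assumed ICCs. At 0.01 they are slight: stunting 78% in UP, with AP still at 81%, and bands 77.5% and 79%. At 0.05 they are material, above all in UP, where stunting has 57% and the bands 65%. Sector-level correlation would lower all of these further.

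As a caveat only: with one district per arm in each state, district-by-time variation cannot be separated from the programme effect. Any restated power is therefore conditional on the named district pairs.

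**What to change.** - Delete the sentence that dismisses the design effect.
- Estimate the ICC or design effect of each primary outcome from the baseline survey, at AWC and sector level. The cohort section already cites a baseline result, so the data should be at hand.
- Restate Table 2.1 at the fixed sample sizes, as power or detectable difference, separately for UP (60 AWCs) and AP (110 AWCs).
- Add one sentence that the power statement is conditional on the named district pairs.

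To show what the restated table might look like at assumed AWC-level ICCs of 0.01, 0.02 and 0.05: for stunting, 2.8016 × √(DE × 0.4884/1200) gives 6.2, 6.6 and 7.9 percentage points in UP and 5.9, 6.2 and 6.9 in AP. For a z-score band, 2.8016 × √(DE × 2.42/600) gives 0.19, 0.19 and 0.21 in UP and 0.18, 0.19 and 0.20 in AP.

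The cost is a rerun of one table and a change of wording, with no extra respondents. The downside is that the stated detectable differences become less favourable.

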NFHS-2 reports that the prevalence of anemia among children aged 12-23 months nationally was 77.7% (children aged <3 years: 74.3% nationally, 73.9% in Uttar Pradesh, and 72.3% in Andhra Pradesh). We estimate that a sample of 772 children could detect a 6% reduction in anemia from the assumed 80% prevalence at baseline among children aged 12-23 months. However, recruitment for hemoglobin assessment includes all children 12-23 months of age who will be enrolled in the surveys for anthropometry and an interview, yielding a larger sample. For women of reproductive age, the prevalence of anemia was 51.8% nationally (48.7% in Uttar Pradesh and 49.8% in Andhra Pradesh). We estimate a minimum sample size requirement of 633 (~800) pregnant women to detect a 8% reduction in anemia prevalence.

Sample size for adequacy surveys

For the 2 adequacy surveys, we target 100 currently pregnant women and 500 mothers of children 0-23 months of age for interviews. The purpose of the adequacy surveys is to monitor the progress and implementation of the INHP-II intervention for various process indicators (e.g., home visits received, antenatal iron-folic acid supplements received), and statistical power is not a primary consideration in sample size estimation. However, we estimate the required sample size of at least 97 currently pregnant women to estimate the process indicators with 10% margin-of-error, and round the sample size to 100 pregnant women for the adequacy surveys. With a target sample of 500 mothers of children 0-23 months, we expect to detect at least a 9% difference in program coverage between the arms.

Based on population size, we need 24 and 13 AWC areas in AP and UP districts, respectively, to meet the sample size requirements.

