In all districts, one sector will be randomly sampled from each block for selection of the Adequacy Survey sample. In AP districts, 2-3 AWC per sector will be sampled in proportion to the number of AWC per block for a total of 24 selected AWC areas. In UP districts, 1-2 AWC per sector will be sampled in the same manner for a total of 13 selected AWC areas. The same sample of AWC areas will be used for both adequacy survey rounds to allow for tracking of program exposures in the same AWCs over time.

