**Data Collection**

The evaluation involve 4 rounds of cross-sectional survey data collection: the baseline survey in January-February 2004, the Adequacy I survey in January 2005, the Adequacy II survey in July-August 2005, and the endline survey in January-March 2006. At each survey round, we will conduct interviews with currently pregnant women and mothers of children 0-23 months of age. Anthropometric measures of weight and height/length will be obtained at the baseline and endline surveys. Hemoglobin measurement for assessment of anemia will be carried out among currently pregnant women and children 12-23 months of age at the baseline and endline surveys only. The surveys will be implemented by TNS with guidance from Johns Hopkins and CARE India investigators.

House listing

A hired survey research firm will conduct a household listing operation in all the sampled AWC areas selected for the samples at each survey round. The purpose of the household listing is to identify households with eligible women and children only. If more than one pregnant woman or mother of a child 0-23 months of age will be identified in a household, interviewers will select one eligible woman randomly from that household. The sample of AWC areas are selected with the expectation of identifying at least 2,400 mothers of children 0-23 months of age and 800 currently pregnant women in each district. For the adequacy surveys, the sample targets will be 500 mothers of children 0-23 months of age and 100 currently pregnant women. However, all eligible women from sampled AWC areas will be recruited for survey enrollment.

Training and field work

Training of interviewers and supervisors for each survey round will be carried out by TNS with on-site technical guidance from JHU, KGMU and CARE personnel. The interview teams will be of 4 interviewers, 1 supervisor and 1 field editor each. There will be six teams per state. The supervisors will be trained to take the weight and height/length measurements from women and children, and to collect a fingerprick blood sample for hemoglobin assessment. The interviewers and field editors will be trained to assist in both these tasks. The JHU field office in Lucknow will organize, train, and manage independent quality control teams to supervise the TNS interview teams and assure data quality. The surveys in Uttar Pradesh and Andhra Pradesh will be conducted simultaneously at all survey rounds.

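### The adequacy surveys' 9-point detectable coverage difference for mothers assumes simple random sampling, although each district's sample is all eligible mothers in only 13 (UP) or 24 (AP) AWCs

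*Protocol*

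**What the plan says.** In the Protocol's sample size section, the part on adequacy surveys sets targets of 500 mothers of children 0-23 months and 100 pregnant women. It makes two precision statements. For mothers: "we expect to detect at least a 9% difference in program coverage between the arms". For pregnant women, the requirement is "at least 97 currently pregnant women to estimate the process indicators with 10% margin-of-error", rounded to 100. The same part says the surveys exist to monitor implementation and that power is not a main driver of their size.

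The number of AWCs is derived from population size alone: "we need 24 and 13 AWC areas in AP and UP districts, respectively, to meet the sample size requirements". Under Sample Selection, one sector is drawn per block. For AP, "2-3 AWC per sector will be sampled in proportion to the number of AWC per block for a total of 24 selected AWC areas". For UP, "In UP districts, 1-2 AWC per sector will be sampled in the same manner for a total of 13 selected AWC areas". The same AWCs serve both rounds. The house-listing part of Data Collection repeats the targets ("For the adequacy surveys, the sample targets will be 500 mothers of children 0-23 months of age and 100 currently pregnant women") and says every eligible woman in a sampled AWC area is to be recruited.

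The only statement on design effect stands in the baseline and endline part. It says none is applied because in nutrition studies it has been negligible. The adequacy part mentions neither a design effect nor an ICC.

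**The concern.** The 9-point figure treats 500 mothers as 500 independent observations. They are a take-all sample of a small number of AWCs. The adequacy indicators are services received, such as home visits and antenatal iron-folic acid. The Protocol describes delivery that is organised by AWC: one worker manages each centre, and Nutrition and Health Days and community organisations are features of the individual AWC. Women in one AWC are therefore likely to resemble each other in coverage, and an argument about anthropometry or anemia does not carry over to that outcome.

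The Protocol plans no mid-term evaluation and relies on the cohort and the process evaluation instead. The cohort is in UP only, so in AP the adequacy surveys are the main interim survey comparison of coverage between arms. A reader who trusts the 9-point figure could take the absence of a visible gap as evidence of similar coverage when the survey had limited ability to show one.

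**Working it through.** **Inputs from the Protocol.** 500 mothers, read as per district; 13 AWCs per UP district and 24 per AP district; all eligible women taken in each. Alpha 0.05 and "a statistical power of 80% to detect a difference" are stated for the baseline and endline surveys and are assumed to carry over, two-sided.

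**Assumptions.** Coverage near 50%. The documents give no ICC, so 0.01, 0.05 and 0.10 are shown.

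**Reproducing the plan's figures.**
- Mothers: (1.96 + 0.84) × √(2 × 0.25 / 500) = 0.089. Solving the pooled two-proportion power formula gives 8.8 points, or 9.0 with continuity correction. The n per arm for 50% vs 59% is 480 (502 with correction), and power at 500 per arm is 82%. The stated 9 points is therefore the figure for a design effect of 1. The match also supports reading 500 as per district.
- Pregnant women: 1.96² × 0.25 / 0.10² = 96.04, rounded up to 97.

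**Adding AWC clustering for mothers.** Design effect = 1 + (m − 1) × ICC, with m = 500/13 = 38.5 in UP and 500/24 = 20.8 in AP. Effective n = 500 / design effect. The detectable difference solves the pooled two-proportion formula at 80% power with the lower coverage at 45.5%. Power is for 50% vs 59%.

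| State | ICC (assumed) | Design effect | Effective n per arm | Detectable difference | Power for 9 points |
|---|---|---|---|---|---|
| UP | 0.01 | 1.37 | 364 | 10.4 | 68% |
| UP | 0.05 | 2.87 | 174 | 14.9 | 39% |
| UP | 0.10 | 4.75 | 105 | 19.1 | 26% |
| AP | 0.01 | 1.20 | 417 | 9.7 | 74% |
| AP | 0.05 | 1.99 | 251 | 12.5 | 53% |
| AP | 0.10 | 2.98 | 168 | 15.2 | 38% |

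**Slack in the claim.** Keeping 80% power for 50% vs 59% requires an effective n of 480, so a design effect of at most 500/480 = 1.042. That allows an ICC of 0.042/37.5 = 0.001 in UP and 0.042/19.8 = 0.002 in AP.

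**Not included.** The sector stage is ignored. Using t in place of normal quantiles for so few AWCs would add about 4% (UP) or 2% (AP) to the detectable difference.

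**Pregnant women.** Because recruitment is take-all, the expected yield matters more than the target of 100. The cohort's Sampling Strategy section reports 12.2 pregnant women per AWC at the UP baseline, so 13 × 12.2 ≈ 159. In AP, 800 expected from 110 AWCs is 7.3 each, so 24 AWCs yield about 175. A margin of 10% allows a design effect of n × 0.10² / (1.96² × 0.25):
- UP: 1.586/0.960 = 1.65, so ICC up to 0.65/11.2 ≈ 0.06.
- AP: 1.745/0.960 = 1.82, so ICC up to 0.82/6.27 ≈ 0.13.

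**The case against.** The strongest reply is that these are monitoring surveys. The Protocol says power is not their main consideration and attaches no test, threshold or decision rule to them. Reusing the same AWCs to follow exposure over time is a purpose that the 9-point figure does not describe, and the process evaluation also includes report abstraction. This stands, and it lowers the severity. It does not make a stated detectable difference correct.

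A second reply is that no ICC is documented and that clustering may be modest. Auxiliary nurse midwives also deliver services, and change agents each cover 15-20 families, so exposure varies within an AWC as well. That is fair, and it is why a range is shown. Still, at an ICC of only 0.01, power for 9 points is already 68% (UP) and 74% (AP). Coverage near 50% is the least favourable case, but it is also the one that reproduces the plan's figure.

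A reader might infer more than the documents support:
- **That precision is roughly halved.** For mothers, doubling the detectable difference needs a design effect of 4, hence an ICC of about 0.08 in UP (3/37.5) or 0.15 in AP (3/19.8). Neither value can be established from the documents.
- **That the 10% margin for pregnant women fails equally.** It does not. With the expected yields it survives a moderate ICC in both states.
- **That the surveys will report false gaps.** The Protocol prescribes no unadjusted test here, and the analysis may be specified in a statistical analysis plan that is not at hand.

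**Conclusion.** The concern holds for the mothers' coverage comparison. The arithmetic behind 9 points is right for simple random samples, but the sampling design does not deliver it unless the AWC-level ICC of coverage is practically zero. The shortfall is larger in UP, where fewer and larger clusters are used. Across assumed ICCs of 0.01 to 0.10 the detectable difference is about 10 to 19 points in UP and 10 to 15 in AP. These figures rest on coverage near 50%, 500 mothers per district, equal AWC sizes, and alpha and power carried over from the main surveys.

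For pregnant women the omission of clustering is a minor point: the stated margin is met up to an ICC of about 0.06 in UP and 0.13 in AP. Overall severity is low.

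**What to change.** Replace the single 9% figure with a cluster-adjusted detectable difference for each state. Base it on the AWC-level ICC of coverage indicators estimated from the baseline survey, whose questionnaires already cover antenatal care, supplementation and provider contacts in 60 (UP) or 110 (AP) AWCs per district. Until that estimate is available, show a range over assumed ICCs. State that the between-arm coverage comparison will use AWC-clustered intervals. For pregnant women, keep the 10% margin and add the expected yield and the ICC it assumes.

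The cost is one ICC estimation from data already planned and a few sentences of text. No extra interviews are needed. The downside is a less favourable stated figure.
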